### Recruitment

Participants will be identified and selected from the staff and students of the Mashhad University of Medical Sciences who volunteer to participate in the study.

### Assignment of interventions: allocation

#### Sequence generation

As the present study is a crossover study, all participants will receive both interventions. In the present study, only the intervention initiation meal will be randomized. Participants will be randomly allocated to AP or PP conditions based on a 1:1 ratio (simple randomization). The randomization will be performed using a random number table. A random sequence will be generated and sealed in envelopes by a person who is not a member of the research team. Each participant will randomly choose an envelope to be allocated to one of the two test meal conditions for the first trial. Then, the participants will receive the other test meal in the next trial after a 1-week washout period.

#### Concealment mechanism

As participants consume both the protein meals, allocation concealment will be done to identify the sequence of test meal intake.

#### Implementation

Generation of the allocation sequence, enrolment of participants, and assignment of participants to interventions will be done by a person who is not a member of the research team.

### Assignment of interventions: blinding

#### Who will be blinded?

Not blinded.

#### Procedure for unbinding if needed

Not blinded.

## Data collection and management

### Plans for assessment and collection of outcomes

#### Indirect calorimetry

RMR (kcal/d), DIT (kcal/d), and SO (g/d) will be measured by IC. To do calorimetry, participants will be asked to lie down in the supine position while awake and immobile; then, air samples will be collected using a mask (MetaLyzer 3B-R3 device), and respiratory gas (O_2_ and CO_2_) exchange will be measured for 20 min in the fasting phase, followed by postprandial measurements 60, 180, and 300 min after consumption of the test meals. The IC will be calibrated before the start of the measures.

The respiratory quotient (RQ) is the ratio of VCO_2_ to VO_2_ (VCO_2_/VO_2_), which reflects the rate of SO. DIT is the production of heat related to SO during energy uptake. DIT varies according to the quantity and type of oxidized substrate (i.e., carbohydrates, proteins, and fat).

IC will be performed in a quiet area at room temperature and mild lighting and require specific conditions (i.e., free of physical activity and psychological stress, fasting state for more than 6 h before the measurement, and resting in the supine position for > 20 min before the calorimetry). During the measurement, the room temperature will be maintained between 23 and 25 °C.

Given that stress has a negative effect on the quality of the calorimetry, the following measures will be taken to minimize the stress level of the participants:Performing the test in a completely quiet roomProviding facilities for the participants to rest in the intervals between assessments and at least half an hour resting before the testIn case of determining stress and tension in participants, testing will be postponed to another day

#### Pulse wave analysis and pulse wave velocity

An ultrasound evaluation of the carotid artery will be done in the supine position, with the head turned 45° away from the scanning side. PWA and blood pressure measurement will be conducted using the Sphygmocor XCEL device on the right side of each participant. Blood pressure will be measured after at least 15 min of rest on the right upper arm. Moreover, the measurement of augmentation index (AIx), central blood pressure (cBP), and heart rate (HR) will be done according to the manufacturer’s guidelines for pulse wave analysis. As AIx is inherently heart rate dependent, the AIx75, which standardizes AIx to a heart rate of 75 beats per minute, will also be used.

Furthermore, arterial stiffness measurement will be taken using the tonometer at the femoral and carotid arteries, which give carotid-femoral PWV.

PWV will be examined according the sequentially measured electrocardiogram-gated left carotid and radial waveforms (applanation tonometry) using the stepwise method. The travel distance of the pulse wave will be calculated as the distance from the suprasternal notch to the femoral artery and the distance from the suprasternal notch to the carotid artery using a flexible tape measure. The measurements will be performed at least twice, and the mean PWV will be applied to the analysis. PWV will be measured at baseline and 30, 90, 210, and 330 min after the test meals.

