**Fig. 1 Fig1:**
[figure not shown]
Study diagram of enrollment, interventions, and assessments

Participants will be instructed not to drink alcohol or engage in severe physical activity within 48 h before each test day. Participants will not be allowed to fast the day before the test days. On the morning of the test day, participants will travel to the research center at Imam Reza Hospital by taxi (with a minimum activity) to arrive at 7 a.m. Participants should abstain from food, drinks (except water), alcohol, and caffeine for 12 h.

On arrival, anthropometric parameters will be measured, and an intravenous catheter will be inserted into an antecubital arm vein. Before consuming the test meals, fasting measurements of indirect calorimetry (IC), PWV and PWA, and subjective appetite will be performed, and venous blood will be collected via the intravenous catheter. Then, participants will be given 15 min to eat the test meals under the researcher’s supervision until the test meal is wholly consumed.

Afterward, postprandial phase tests, including IC, PWA, PWV, and assessing the appetite response, will be performed. Blood samples will also be collected within 6 h. All the tests will be performed in the same conditions (e.g., quiet and temperature-regulated room).

Figure 2 depicts the schedule of the study days. Time points were determined according to the preliminary results of our previous study. The testing conditions will be repeated on the next test day.

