#### Provisions for post-trial care

A physician and nurse will be present, and the participants’ symptoms will be checked during the project (6 to 8 h). After removing the catheter, blood pressure, puncture site bleeding, and other symptoms, such as dizziness, will be checked.

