### Outcomes

The primary outcome of this trial will be the comparison of the acute effects of the two test meals on appetite response, and energy metabolism parameters, including resting energy expenditure (REE), DIT, and SO, and arterial stiffness indices (PWV and PWA) in overweight and obese men.

The secondary outcome is to compare the effects of two test meals on postprandial lipemia, including free fatty acids (FFA), low-density lipoprotein (LDL), high-density lipoprotein (HDL), total cholesterol (TC), and triglycerides (TG), glycemia (blood glucose), and insulinemia (serum insulin) in overweight and obese men.

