#### Strategies to promote participant retention and complete follow-up

On the two test days, the researcher will be present at all stages of the study and measurements and will monitor the study process. Phone calls will be arranged to remind participants regarding the next test appointment.

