#### Data management

In the current study, the database will be generated from IC, Sphygmocor XCEL, and laboratory assay results in the Excel software and SAS software version 9.4. To increase the accuracy of data collection, all data will be collected by principal investigators. Finally, data will be analyzed using the SAS software. For data security, usernames and passwords will be provided only to the study researchers.

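### PWV, a primary outcome, is taken by investigators not blinded to the meal, with no upper limit on the readings that enter the mean, so a repeat habit that differs by meal would bias the contrast

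*Protocol article*

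**What the plan says.** The Outcomes section of the protocol article counts "arterial stiffness indices (PWV and PWA) in overweight and obese men" within the primary outcome.

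The section on pulse wave analysis and pulse wave velocity describes the method: "arterial stiffness measurement will be taken using the tonometer at the femoral and carotid arteries, which give carotid-femoral PWV". The path length is measured by tape. The schedule is "PWV will be measured at baseline and 30, 90, 210, and 330 min after the test meals", and the rule on replicates is "The measurements will be performed at least twice, and the mean PWV will be applied to the analysis". No maximum, agreement criterion or quality trigger follows.

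On who does what:
- The blinding section answers that no one is blinded and makes no exception for outcome assessors.
- Data management: "To increase the accuracy of data collection, all data will be collected by principal investigators".
- Trial design: "participants will be given 15 min to eat the test meals under the researcher’s supervision until the test meal is wholly consumed".
- Retention section: "the researcher will be present at all stages of the study and measurements and will monitor the study process".
- Post-trial care section: "A physician and nurse will be present".

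**The concern.** Tonometry depends on the operator, who places the probe, accepts or rejects the waveform and decides whether to repeat. If that person knows which meal was eaten and may stop after two readings or go on, the decision to repeat can depend on whether the running mean looks right. This is a stopping rule that depends on the result. Even though every reading is averaged, the expected mean moves towards whatever the operator regards as plausible for that meal.

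Participants cannot be blinded to a chicken, egg and yogurt meal versus a soy meal. That does not oblige the tonometer operator or the analyst to know the meal. The Discussion argues that the controlled setting allows differences to be attributed to the protein source. That inference weakens if the measurement process can itself depend on the meal. The problem arises when the data are collected, so a later analysis plan cannot repair it.

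**Working it through.** **The plan's own figure.** The only calculated figure in the article is the sample size, and it rests on resting energy expenditure: m = 2(1.96 + 0.84)² × 330² × [1 + 4(1 − 0.5)] / (4 × 250²) = 20.49, rounded up to 21, as stated. It says nothing about PWV. No PWV effect, SD or repeatability is given, so every m/s value below is an assumption.

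**Inputs**
- Completers: 46 less the planned 10% dropout, 46 × 0.9 = 41.4, taken as 41.
- Two-sided α = 0.05, from the sample-size section.
- Single-reading SD s = 0.5 m/s (assumed).
- SD of the paired meal difference = 0.6 to 0.8 m/s (assumed).
- Operator habit (assumed): after two readings, add a third if their mean lies on the unfavoured side of the true value, then average all three.

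**Step 1: shift in the mean for one meal.** The mean of two readings has SD s/√2. Its expected contribution from the unfavoured side is 0.399 × s/√2 (0.399 is the standard normal density at 0). Adding a third, unbiased reading shrinks that part by one third.

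Shift = (1/3) × 0.399 × s/√2 = 0.094 s.

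A simulation of one million measurement sets gave 0.095 s. With exactly two readings it gave 0, apart from simulation error. Because the plan sets no cap, the same habit carried to at most 4 or 6 readings was also simulated; the shift was 0.15 s and 0.20 s.

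**Step 2: shift in the meal contrast at s = 0.5 m/s, at most three readings**
- Habit on one meal only: 0.094 × 0.5 = 0.047 m/s.
- Meals pushed in opposite directions: 2 × 0.047 = 0.094 m/s (0.19 s).
- Opposite pushes in one session in four: 0.094 / 4 = 0.0235 m/s.
- Same habit on both meals: the shifts cancel within each man, giving 0.

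**Step 3: type I error.** SE = SD/√41, which is 0.0937 at SD 0.6 and 0.1249 at SD 0.8. With k = shift/SE, type I error = 1 − Φ(1.96 − k) + Φ(−1.96 − k).

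| Scenario | k at SD 0.6 | Type I error | k at SD 0.8 | Type I error |
|---|---|---|---|---|
| One meal affected | 0.50 | 7.9% | 0.38 | 6.6% |
| Opposite pushes | 1.00 | 17.1% | 0.75 | 11.7% |
| Opposite pushes, one session in four | 0.25 | 5.7% | 0.19 | 5.4% |

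**Check on the SD range.** At s = 0.5 m/s under the opposite-push rule, measurement error alone gives a paired-difference SD of about 0.45 m/s at a single time point, before any day-to-day variation. A paired SD of 0.4 m/s is therefore not attainable there, and error rates computed from it should not be used.

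**The case against.** Four points have force.

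1. A reader might infer that one person both supervises the meal and holds the tonometer. The documents do not say so. The meal is supervised by the researcher, who is then described as present and monitoring, while data collection is assigned to principal investigators in the plural. This stands. It does not remove the risk, because nobody is blinded whoever holds the device.

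2. A reader might also infer drift towards an expected meal effect. No direction for PWV is stated: the Background calls the data scarce, and the rationale expects a difference without giving its sign. A direction can be pieced together only indirectly (animal protein lowering lipemia in some studies, lipemia affecting stiffness). This stands too, and a habit common to both meals cancels.

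3. The error rates describe a consistent habit with a trigger at each man's true PWV, which no operator knows. Nothing in the text suggests that anyone intends to repeat readings selectively. An identical push at baseline would also partly cancel in change scores. The figures are illustrations towards the upper end, not predictions.

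4. Averaging replicates is sound, and a journal article may leave the trigger for a third reading to a device procedure. This has some weight against the replicate rule taken alone. It does not answer the combination: the article itself states an open-ended count, data collection by the investigators and no blinding. Followed exactly, it leaves the count to someone who may know the meal.

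**Conclusion.** The point holds as a weakness in how a primary outcome is collected: an operator-dependent measurement, no blinding of assessors, and an open-ended number of readings in the mean. The documents do not show that bias will occur, in which direction, or by how much.

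On the stated assumptions (41 completers, reading SD 0.5 m/s, paired-difference SD 0.6–0.8 m/s, at most three readings), a nominal 5% test would run at about 7–8% if one meal is affected and 12–17% if the meals are pushed in opposite directions. It stays close to 5% if the habit is rare. The change is worth making because it is cheap and the article says that enrolment has not begun.

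**What to change.** In the PWV section, set the number of readings per time point at two. Allow one further reading only under a preset agreement or device-quality rule, applied identically at every time point and visit, and name one summary of all accepted readings. The agreement limit should come from the device's known repeatability; the documents supply no value.

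In the blinding and data management sections, state that the PWV/PWA operator is kept unaware of the meal where feasible. For example, a staff member already on site could supervise the 15-minute meal while the operator is out of the room. State also that the analyst receives the meals coded X and Y until the main analysis is fixed. Fixing the count alone is not enough, because it leaves probe placement and waveform acceptance open to an operator who knows the meal. Specimens need no change: the Confidentiality section already provides for coded IDs.

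The cost is protocol wording and a change in who watches the meal. The downside is that a participant may reveal what he ate, so operator blinding may be imperfect.

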#### Appetite response

During the test day, participants will be given a paper-based questionnaire before and every 1 h after the test meal to record their feelings of hunger and satiety. Appetite questions are assessed based on (a) satiety score card, (b) visual analog scale, (c) satiety labeled intensity magnitude scale, (d) unlabeled visual hunger/fullness category scale, and (e) “Teddy the Bear” hunger and satiety rating scale. The calculated score represents the most extreme sensation the participant had experienced and the response options or satiety or motivation-to-eat in a wide range to be well expressed.

#### Blood samples

Blood samples will be collected before and 60, 120, 180, and 300 min after meal consumption to evaluate metabolic markers. A maximum of 2 ml of blood will be collected from each participant at each of the given times (overall 10 ml/day) to measure glucose, insulin, TG, LDL, HDL, TC, and FFAs. The blood samples will be centrifuged immediately, and the serum samples will be stored at − 20 °C. On each test day, measurements will be taken from 7 a.m. till 2 p.m.; we selected this period because it was supposed to represent a typica1 interval between breakfast and lunch.

#### Anthropometric parameters and body composition

The anthropometric parameters will be measured at the beginning of the study by a trained nutritionist. Body weight will be measured on a clinical scale (SECA) to the nearest 0.1 kg. Height will be measured with a wall-mounted stadiometer to the nearest 0.1 cm. Based on the obtained measurements, BMI will be calculated (weight (kg)/height (m^2^). Waist circumference will be measured at the midline between the lower border of the ribs and the iliac crest in a horizontal plane to the nearest 0.5 cm. Finally, the body composition of the participants will be analyzed using bioelectrical impedance analysis (InBody 270-Waynesboro YMCA).

#### Dietary measurements

A 3-day food record will be collected from all participants at baseline. Moreover, dietary intakes will be assessed using a 24-h dietary recall on each test day; the collected data will be analyzed by the nutritionist 4 software.

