### Trial design

This is an acute randomized crossover clinical trial study of two protein-based breakfast meals with different protein sources (AP and PP). Each participant will consume two different test meals on different days with a 1-week washout period in between. Figure 1 shows the diagram of enrollment, intervention, and assessments.

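### Eating on the day before each test day is recorded but not matched between the two visits, a small and cheaply removed source of within-man variance

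*Protocol article*

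**What the plan says.** The Trial design section sets out a two-period crossover: "Each participant will consume two different test meals on different days with a 1-week washout period in between". The text below Fig. 1 lists how men prepare:

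- Alcohol and hard exercise are ruled out for 48 h ahead of both visits.
- On the previous day's eating: "Participants will not be allowed to fast the day before the test days"
- On the overnight fast: "Participants should abstain from food, drinks (except water), alcohol, and caffeine for 12 h"

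They travel by taxi and arrive at 7 a.m. After the test-day procedures comes the sentence "The testing conditions will be repeated on the next test day".

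Under Dietary measurements, "A 3-day food record will be collected from all participants at baseline", and "dietary intakes will be assessed using a 24-h dietary recall on each test day". Table 1, as it reads here, ticks the 24-h recall only in the Time 0 (allocation) column and not at either intervention visit. The statistical methods section names time and protein source as the model effects and does not mention the recall. The retention section adds that "Phone calls will be arranged to remind participants regarding the next test appointment".

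**The concern.** Each man is his own control, so what differs within a man between the two mornings, other than the meal, is noise in the AP-PP contrast. The protocol evidently regards pre-visit behaviour as relevant, since it restricts alcohol, exercise and the fasting window. What and how much a man eats the day before is left free, apart from the bar on fasting.

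A man could eat a large, fatty or carbohydrate-rich evening meal before one visit and a light one before the other. After a 12-h fast this could still shift substrate oxidation/RQ, triglycerides, FFA, glucose, insulin and appetite. That mechanism is general physiological reasoning; the documents do not quantify it. What is at stake is some of the precision that a crossover is chosen for, in outcomes the plan did not size.

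**Working it through.** **1. Is prior-day diet fixed or repeated anywhere?** The rules below Fig. 1 cover alcohol, activity, a bar on fasting the day before, the 12-h fast and travel. The sentence on repeating testing conditions follows the test-day procedures and room conditions and does not name diet. Dietary measurements records intake only. No section supplies a meal or asks for a repeat.

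**2. The plan's own sample-size figure.** Inputs from Sample size: difference 250, SD 330 kcal/day, correlation 0.5, 4 measurements, z-values 1.96 and 0.84.

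m = 2 × (1.96 + 0.84)² × 330² × [1 + 4(1 − 0.5)] / (4 × 250²) = 20.49, so 21. Adding 10%: 21 × 1.1 = 23.1. The stated 21 and about 23 per group (46 in all) reproduce.

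**3. What matching could gain.** The variance of a paired difference is twice the within-man variance, so the standard error scales with the within-man SD. If a share f of that variance came from prior-day diet and were removed completely, the standard error would fall by 1 − √(1 − f). The share f is an assumption; the documents give none.

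**4. What that means for REE.** Assumptions: 46 × 0.9 = 41.4, so 41 completers; SD of the paired difference 330 kcal/day. The 330 may be read as that SD directly, or as a per-condition SD with correlation 0.5, since 330 × √(2 × (1 − 0.5)) = 330. The detectable difference at 80% power is about (1.96 + 0.84) × SD / √41. Power is from the noncentral t with 40 degrees of freedom.

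| Share f removed | Fall in standard error | SD of difference | Detectable difference | Power, 250 kcal/day | Power, 150 kcal/day |
|---|---|---|---|---|---|
| 0 | 0 | 330 | 144 | 99.7% | 81.1% |
| 5% | 2.5% | 322 | 141 | 99.8% | 83.0% |
| 10% | 5.1% | 313 | 137 | 99.9% | 84.9% |
| 20% | 10.6% | 295 | 129 | >99.9% | 88.8% |

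Sensitivity: with 330 as a per-condition SD and correlation 0.3, the SD of the difference is 390.5 and power for 250 kcal/day with nothing removed is still 97.9%.

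**5. Part of the effect is already removable.** Calorimetry, PWV/PWA, appetite and blood are all measured fasting at each visit. A prior-day effect that shifts the fasting and postprandial values alike would largely cancel in a change from fasting or a baseline-adjusted model. The falls in step 3 are therefore upper bounds for each assumed f.

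**The case against.** The strongest reply is that nothing here is misstated: preparation sheets and call scripts are detail that an article leaves to the full protocol, and covariate choice belongs in an analysis plan. The covariate part of that reply stands, so the absence of a model term is not held against the plan. The rest carries less weight, because the article does list its preparation rules, down to taxi travel, and a diet repeat is not among them. Excluding irregular breakfast eaters and men with dietary restrictions may limit erratic eating, but it does not match the two days.

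Three stronger readings are tempting, and the documents do not support them.

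- *Every paired comparison is materially degraded.* The visit-specific fasting values take up part of the effect, and nothing in the documents shows that prior-day intake affects PWV, PWA, LDL, HDL or total cholesterol after a 12-h fast.
- *The AP-PP contrast is biased.* Meal order is randomised, so this is in expectation a loss of precision. The trial is unblinded and men could know which meal comes second, so eating in anticipation of it is possible, but nothing shows that it would happen.
- *Matching is worth a quarter more men.* That is 1/(1 − 0.20) − 1 = 25%. It takes the top of an assumed range and supposes that free-living men repeat a day perfectly.

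Any gain also arises only in within-man analyses. The statistical section also names independent t tests and, in one branch, a first-period comparison; matching diets across visits does nothing for those.

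**Conclusion.** The point holds as a cheap improvement, not as an error that threatens the trial. Prior-day intake is recorded but left unmatched, and it can add within-man variance, most plausibly to substrate oxidation/RQ, triglycerides, FFA, glucose, insulin and appetite. The size cannot be derived from the documents. Under assumed shares of 5% to 20%, removed completely, the standard error falls by at most 2.5% to 10.6%.

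The planned 250 kcal/day REE comparison is essentially unaffected in a paired analysis, and the 46 men need not change. Any benefit lies in smaller REE differences and in outcomes that were not sized. Separately, Table 1 and Dietary measurements disagree on when the recall is taken, and the remedy depends on its being taken at the visits.

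**What to change.** 1. In Trial design, beside the other preparation rules, state that each man receives a copy of his visit-1 24-h recall and is asked to repeat that day's intake, at least the evening meal, before visit 2. This presumes that the recall covers the day before the visit; say so explicitly.
2. Add a reminder to the phone call already planned.
3. Tick the 24-h recall at both intervention visits in Table 1, in line with Dietary measurements. The second recall then shows how well the repeat was followed.
4. Optionally, use prior-day energy intake as a visit-level covariate in a supporting analysis only.

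The cost is one sheet, one sentence in an existing call and a small participant burden for one day. No men, visits or assays are added. According to Trial status, enrolment had not begun when this version was written.
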